#### CR program delivery by health technology using an empowerment approach

The 12-week CR program is the core component of the intervention and aims at using two core methods including an interactive and motivational web platform, and a tele-care platform to optimize CR participation and behavioral modification.

The interactive and motivational web-based platform consists of three key platforms: a) self- monitoring with motivational feedback platform, b) an interactive and experiential learning platform, and c) health dialogue forum. The design of this platform followed the guideline of the Health Literacy Online to improve the comprehensiveness and utility of the content [55]. The content was revised to be at the readability level of sixth to ninth grade examined by Microsoft® Word® Office Package (Microsoft Corp, Redmond, WA) to optimize comprehension. The web platform can be automatically adjusted to computer and smartphone interfaces to improve flexibility and access.

#### Self- monitoring with motivational feedback platform

The self-monitoring page will document the goals and action plans developed for improving exercise level, dietary habits, stress management and/ or tobacco cessation during the preparatory phase. Participants are recommended to input self-monitoring data on a daily/weekly basis to indicate the level of goal attainment. For exercise, participants will upload exercise times, the intensity level as light/moderate/vigorous and the duration of engagement in 1 week. In addition, the guidelines for CR also recommend a higher level of walking to exceed 7000 steps [56], and each participant will be encouraged to upload their daily step count measured by their pedometer. Participants will be encouraged to complete the guideline based dietary habit checklist and their score on the 0 to 9 stress scale to indicate their dietary habit and stress level. A traffic light system will be used to give motivational feedback based on the level of goal attainment, with red indicating attention required (< 50% of goal attainment), yellow representing moderate achievement (> 50–90% of goal attainment) and green indicating full attainment (90–100% of goal attainment). An automated message which corresponds to the level of goal attainment and shares the trend in participants’ recordings will be presented. Patients will be asked to report on tobacco use and encouraged to update their smoking status (if applicable) with green indicating they have quit while red represents smoking. Based on the pre-determined coding, an overall score on goal attainment will be generated along with the traffic light system to reflect progress on each behavioral change.

#### Interactive and experiential learning platform

The interactive and experiential learning platform provides all intervention group participants access to comprehensive health information regarding CHD. The content was developed according to the updated international guidelines and culturally appropriate national recommendations for CR by the American Heart Association, American Psychological Association, American Diabetes Association, The American Cancer Society, Chinese Nutrition Society, and the National Center for Cardiovascular Disease [42–49]. The content covers the pathophysiology and manifestation of CHD, physical activity, diet management, smoking cessation, stress management, risk factors management (hypertension, cholesterol, and diabetes), symptom management and post-PCI management. The health information has been adapted to fit in the Chinese context, and the content of this platform has been validated by a cardiologist, dietitian and cardiac nurses. To motivate participants, each component is presented sequentially: i) introducing the role and underlying mechanism of each care component in disease management, ii) the required lifestyle changes, iii) recommended actions, and iv) self-monitoring to track progress and resolutions to barriers. Various learning opportunities will be provided using scenario-based case sharing to illustrate behavioral change barriers, challenges and resolution alternatives; videos for skills demonstrations and role modeling; and pictures, slogans and comics to present these sessions in an engaging manner. The health dialogue forum aims at providing a method for posting CR research news and answering questions from participants.

#### Tele-care platform

In the tele-care platform, the nurse will retrieve self-monitoring data uploaded by participants and anonymously share goal attainment of group members as well as discuss their experiences and address any concerns. Reminders for uploading data will be sent to participants weekly. This platform permits participants to contact the nurse about issues or adverse changes in health. The nurse will contact each individual at weeks 2 and 4 post-discharge to assess fitness, explore difficulties, encourage progress and offer solutions. This may lead to revision of the action plan or goal adjustment. Participants will be asked to maintain password and account security, and to avoid discussing of intervention content with other patients in the hospital to avoid contamination.

### Usual care

Participants in the both groups will receive the usual health care information related to maintaining a healthy lifestyle (exercise, diet and smoking cessation), instructions on medication during hospitalization, and one follow-up call. The research nurse will instruct control group participants on use of the pedometer.

### Randomization and data collection procedure

Eligible patients will be invited to participate in this study and an information sheet will be provided. After obtaining informed consent, baseline data will be collected. Participants will be randomly assigned to either the intervention or control group by block randomization. Three different block sizes of 4, 6 and 8 will be used. The random number for group assignment will be generated by random allocation software. The group assignment will be written and placed in an opaque sealed envelope and given to participants by the research assistant after baseline data collection (T_0_). Outcome evaluation will take place at the 6-week intervention (T_1_) and upon completion of the 12-week intervention (T_2_) by trained research assistants who are blinded as to the participants’ intervention allocation (Fig. 1). Participants will not be blinded as to their group allocation. The following parameters for outcome assessment will be used to include health behavior, emotional outcomes, health-related quality of life, cardiac physiological risk parameters and unplanned health services use. Participants’ travel expenses for data collection will be reimbursed.

**Fig. 1 Fig1:**
[figure not shown]
Flow diagram of the study protocol

### Primary outcomes

The primary outcomes focus on health behavioral change including physical activity, health promoting lifestyle habits, and smoking behaviors. Physical activity is defined as movement of the body that uses energy. Objectively, physical activity level will be measured by the pedometer (Mi Band, China) record of step count for three weekdays [57]. A pedometer correlates strongly with different accelerometers (median r = 0.86) as well as the time in observed activity (median r = 0.82) [58]. The International Physical Activity Questionnaire (IPAQ) will be used to comprehensively assess the self-reported time spent in walking, light/moderate/rigorous exercise and sitting across various domains using 27 items. The IPAQ has test–retest reliability with intra-class correlation coefficients of 0·74 to 0·97 for each sub-domain for Chinese adults [59]. Total physical activity measured by the IPAQ was moderately correlated with pedometer measured exercise levels (r = 0.46) [60].

Health promoting behaviors will be measured by the Health Promoting Lifestyle Profile II (HPLP- II) [61]. The HPLP- II measures six aspects of health promotion behaviors including nutrition, interpersonal support, stress management, exercise, health responsibility and self-actualization. The HPLP - II has good internal consistency with 0.92 for the entire scale and 0.69–0.84. The HPLP uses a four-point scale with 1–4 representing always to never with a total score ranging from 40 to 160 and a higher score indicating better health behavior. The HPLP-II has been translated and validated into Chinese with Cronbach’s α coefficient of 0.63 to 0.81 [62].

Smoking status will be asked to evaluate the abstinence rate using two questions: (1) what is your current smoking status? (current smoker, ex-smoker or nonsmoker) (2) How many cigarettes do you smoke per day? [63].

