**Methods:**

This single-blinded two-arm parallel randomized controlled trial will randomize 146 patients from the inpatient cardiovascular units of a hospital in Wuhan, China to receive either the NeCR or the usual care. The NeCR intervention uses a hybrid approach consisting of a brief face-to-face preparatory phase and an empowerment phase delivered by health technology. The preparatory phase aims at identifying self-care needs, developing a goal-oriented patient centered action plan, incorporating a peer support network and orientation to the use of the e-platform. The empowerment phase includes use of the multi-media interactive NeCR for promoting symptom management, monitoring lifestyle changes and offering psychological support. A tele-care platform is also integrated to enhance health care dialogue with health professionals and peer groups. The control group will receive the usual care. An evaluation of lifestyle behavioral changes, self-efficacy, health-related quality of life, anxiety and depression, cardiovascular risk parameters, and unplanned health services use will be conducted at baseline, 6 weeks and 12 weeks post-intervention.

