### Study sample

The study will be conducted at four cardiology units of Tongji Hospital, Wuhan, China where CHD patients are treated conservatively with percutaneous coronary intervention (PCI) or medication and discharged under stable medication regimen. Eligibility requirements of participants are: adults aged 18 years or older; hospitalized for an initial diagnosis of CHD based on angiography or exacerbation of this condition in previously diagnosed cases; anticipated discharge to home; uses a computer and/or smartphone to access the Internet at home, reads and speaks Mandarin; minimum of primary education level; and no prescribed activity or exercise restriction. Exclusion criteria are: a diagnosis of acute psychotic disease/ life-limiting condition; absolute and relative contradictions to exercise testing and training and high risk for exercise prescription according to the American Association of Cardiovascular and Pulmonary Rehabilitation (AACVPR) guideline; and, having auditory, visual, fine motor, or ambulatory disorders.

Referring to a systematic review of studies which examined the effects of tele-cardiac rehabilitation on lifestyle behaviors, health outcomes and quality of life, the effects size on promoting healthy lifestyle is 0.42 to 1.29 so that a medium effect size of 0.5 (with 80% power and .05 significance) is conservatively adopted in this study [38]. The estimated sample size is 146, which takes into consideration an expected attrition rate of 12% based on prior studies with similar post-test time points of 6–12 weeks [31, 39]. Eligible participants will be identified by research nurses from four inpatient cardiac departments of the hospital by reviewing medical records. A second confirmation will be made with the on-site physicians. Eligible participants will then be invited to participate in this study and an information sheet will be provided. After obtaining informed consent, baseline data will be collected.

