### Data analysis

The latest version of SPSS will be used to analyze data with a 5% significance level (two-sided). Treatment evaluation will be performed based on the principle of intention to treat. A generalized estimating equations (GEE) model will be used to compare the differential between the two groups related to each of the outcomes across the time-points, with adjustment for potential confounding variables in order to obtain a more precise estimation of intervention effect. The potential confounding variables will be selected on the basis of clinical judgment and statistical incomparability at baseline. For the smoking behavior as nominal data, the Chi-square test will be used to compare the number of patients who quit smoking between the groups. In addition, the Friedman test will be used to compare the changes in percentage of smoking cessation among the groups over time [73]. Survival analysis, the analysis of time-to-event data will be conducted to describe the length of time from entering the program to an unplanned health services utilization.

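### Several unranked primary measures share one undivided 5% level, while the 146 patients are sized for a single comparison of means

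*Protocol article*

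**What the plan says.** The section Primary outcomes opens with: "The primary outcomes focus on health behavioral change including physical activity, health promoting lifestyle habits, and smoking behaviors". It then assigns four instruments to these domains: pedometer step count and the IPAQ for physical activity, the HPLP-II total for lifestyle, and two questions on smoking status. None is placed first.

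Randomization and data collection procedure sets two post-baseline assessments: T1 at week 6, and T2 "upon completion of the 12-week intervention". Neither is named as primary.

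Data analysis gives one error level for everything: "The latest version of SPSS will be used to analyze data with a 5% significance level (two-sided"). A GEE is planned for each outcome over the time points. Smoking has a Chi-square test between groups, whose visit is not stated, and a Friedman test over time. No order of testing, split of alpha or all-must-succeed rule appears.

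Study sample sizes the trial once. It reports from a systematic review that "the effects size on promoting healthy lifestyle is 0.42 to 1.29", and on that basis "a medium effect size of 0.5 (with 80% power and .05 significance) is conservatively adopted in this study". Then: "The estimated sample size is 146, which takes into consideration an expected attrition rate of 12"%.

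**The concern.** A 5% level and 80% power are properties of one test. If several measures are all primary and nothing says which decides, any one of them reaching p < 0.05 can be reported as a positive trial. The error rate for that claim is then well above 5%. If an adjustment is added later to prevent this, the 80% no longer describes each endpoint.

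This matters more here because participants know their allocation, and the Limitations section itself warns of social desirability bias in the self-reported measures. A favourable result on one self-reported measure among several is a plausible outcome, and the plan gives no rule for interpreting it.

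**Working it through.** **Inputs.** From Study sample: effect 0.5, power 80%, alpha 0.05, 146 randomised, 12% attrition, cited range 0.42 to 1.29. From Data analysis: two-sided 5%. From Primary outcomes: four measures in three domains, and r = 0.46 between IPAQ and pedometer. Assumption: 1:1 allocation, which the article does not state but which fits two arms and block sizes of 4, 6 and 8.

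**Step 1: reproduce 146.** A two-sample t-test with d = 0.5, two-sided alpha 0.05 and 80% power needs 63.8, so 64 per arm, or 128 evaluable. Inflating for attrition: 128 / (1 − 0.12) = 145.5, so 146. The stated figure is correct, and it contains no allowance for more than one test.

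**Step 2: chance of at least one false-positive primary result, one test per measure at 5%.** For k independent tests this is 1 − 0.95^k.

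| Reading | Chance |
|---|---|
| Four measures, independent | 1 − 0.95^4 = 18.5% |
| Four measures, only IPAQ and step count correlated (r = 0.46) | 1 − 0.9082 × 0.95^2 = 18.0% |
| Three domains, independent (IPAQ only supports step count) | 1 − 0.95^3 = 14.3% |

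The 0.9082 is the bivariate normal probability that neither of two test statistics with correlation 0.46 exceeds 1.96 in absolute value. It takes the correlation of the test statistics to equal that of the measures. The article gives no correlation for the other five pairs. If all four measures had a common correlation of 0.7 (an assumption), the figure would be about 13%. Testing each visit separately would raise the figures.

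**Step 3: power with 64 evaluable per arm (t-test).**

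| Effect | Two-sided alpha | Power |
|---|---|---|
| 0.5 | 0.05 | 80.1% |
| 0.5 | 0.05 / 4 = 0.0125 | 61.6% |
| 0.42 | 0.05 | 65.5% |

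The 61.6% is the Bonferroni floor. Holm does better: if all four measures truly had d = 0.5 and a common correlation of 0.46 (assumptions), simulation gives about 72% average power per endpoint.

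**Step 4: smoking.** A standardised mean difference of 0.5 does not describe a quit rate. The article gives neither an expected rate nor a number of smokers, so the 80% cannot be carried over to this primary outcome.

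**The case against.** The strongest reply is that this is a condensed article. A testing order or adjustment is often left to the statistical analysis plan, which is not shown, and Data analysis states a significance level without claiming family-wise control. That is fair as far as it goes. But the article itself fixes several unranked primaries, one undivided 5% level and a one-test sample size. An analysis plan that split alpha would make the stated 80% untrue for each endpoint. Only putting one measure first, or requiring all to succeed, avoids a split; the article states neither, and the second would lower the power for overall success.

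The GEE, with repeated measures and covariate adjustment, may recover some power. The article gives no correlation with which to quantify this, and it would not control the false-positive rate.

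Three stronger readings are tempting and are not supported:

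- *Eight tests, four measures at each of two visits.* A reader might infer this, but a GEE over the time points can give one joint group-by-time test per outcome, and the smoking Chi-square has no stated visit. The figures above therefore rest on one test per measure.
- *A contradictory time point.* The abstract says assessments "will be conducted at baseline, 6 weeks and 12 weeks post-intervention", which could suggest visits after the programme ends. The body fixes T1 and T2 clearly, so this is clerical.
- *An effect size wrongly called conservative.* The value 0.5 is above the cited lower bound of 0.42 but close to it, and the midpoint of the range is (0.42 + 1.29) / 2 = 0.855. The article does not claim to use the lower bound. The word is a judgement, not an error.

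**Conclusion.** The point holds and should be fixed. As written, the plan carries about a 14% to 19% chance of at least one false-positive primary result with independent tests, and about 13% if all four measures are strongly correlated. No reading of the primary family brings it to 5%. The stated 80% power is right for one continuous endpoint at d = 0.5. It falls to about 62% at an equal four-way split of alpha, is somewhat higher under Holm, and is undefined for smoking.

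These figures assume 1:1 allocation, 128 evaluable patients, one test per measure and no gain from covariates or repeated measures. The sample-size arithmetic itself is sound; the fault is the mismatch between one sized test and several unranked primaries.

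**What to change.** Before unblinding, name one primary measure at T2, the end of the 12-week programme. Keep 146 with 80% power at d = 0.5 for that measure. Treat T1 as supportive, and test the remaining measures in a fixed sequence as key secondary outcomes.

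Two candidates, each with a condition:

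- **HPLP-II total.** The effect size in Study sample concerns healthy lifestyle, although it names no instrument, so the match is an inference. Primary outcomes codes the items 1 to 4 from always to never yet says a higher score is better; this must be reconciled first.
- **Step count.** It is the objective measure, which is an advantage with unblinded participants, but d = 0.5 would need justifying for it.

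Alternatively, keep all the primaries under Holm, restate power as below 80% per endpoint, and give smoking its own power statement. It would also help to report power of about 65% at 0.42 as a sensitivity figure and to align the abstract's visit wording with the body.

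The cost of the single-primary option is protocol and registry wording, with no extra patients, and fewer results can be called primary. The cost of the Holm option is a less favourable stated power at 146.

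### The scoring rule for the HPLP-II, a primary outcome, contradicts itself: with always = 1 and never = 4, a higher total means worse behaviour, yet the text says it means better.

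*Protocol article*

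**What the plan says.** The Primary outcomes section of the protocol article names the outcome family: "The primary outcomes focus on health behavioral change including physical activity, health promoting lifestyle habits, and smoking behaviors". The second of these is measured by the HPLP-II, whose content is described as follows: "The HPLP- II measures six aspects of health promotion behaviors including nutrition, interpersonal support, stress management, exercise, health responsibility and self-actualization".

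The scoring rule comes in a single sentence. Its first part gives the item codes: "The HPLP uses a four-point scale with 1–4 representing always to never". With the range and the direction added, the codes 1 to 4 are described as "representing always to never with a total score ranging from 40 to 160 and a higher score indicating better health behavior".

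Neither this section nor Data analysis mentions reverse-worded items or recoding before summation. Data analysis has each outcome compared between groups across the time points by generalized estimating equations (GEE), tested two-sided at 5%.

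**The concern.** The sentence fixes three things: the order of the response anchors, the range of the total, and the direction of interpretation. For items that describe desirable behaviours, the first and third are incompatible under a plain sum. This goes beyond a detail left to a fuller document, because the article states the rule and the rule contradicts itself. The next section shows the contrast: under Secondary outcomes, the quality-of-life items run from 1 for low to 7 for high, and the directions given for self-efficacy and for depression, anxiety and stress fit their descriptions.

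What is at stake is the direction of a primary result. Anyone who builds the database, writes the scoring syntax or reuses the published method has to choose which half of the sentence to follow. One possible choice reports an improvement as a deterioration, or the reverse.

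**Working it through.** **Inputs** (all from the protocol article)
- Item codes: always = 1 to never = 4 (Primary outcomes).
- Total: 40 to 160, higher is better (Primary outcomes).
- Content: health-promoting behaviours in six areas (Primary outcomes).
- Design figures: effect size 0.5, 80% power, significance level .05, attrition 12%, total 146 (Study sample); two-sided test (Data analysis).
- Assumptions: all items are worded as healthy behaviours and share one coding; equal allocation, since no ratio is stated.

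**1. Reproduce the range.** With k items each scored 1 to 4 and summed, the minimum is k × 1 and the maximum k × 4. From the minimum, k = 40/1 = 40. From the maximum, k = 160/4 = 40. The two agree, so the stated range is a plain sum of 40 items. It is the same whichever way the anchors run.

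**2. Check the direction.**

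| Respondent | Total with printed anchors | Total with each item recoded as 5 − x |
|---|---|---|
| Always, every item | 40 × 1 = 40 | 40 × 4 = 160 |
| Never, every item | 40 × 4 = 160 | 40 × 1 = 40 |

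Only the right-hand column agrees with the statement that higher is better.

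**3. Effect on the treatment comparison.** Let S be the raw sum. Recoding every item gives Σ(5 − x) = 5 × 40 − S = 200 − S. For any two groups, (200 − S₁) − (200 − S₂) = −(S₁ − S₂). The difference changes sign, while its absolute size, standard deviation and standard error stay the same. In a GEE model that is linear in the total, the two-sided p-value is therefore also the same.

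**4. Would routine checks catch it?** Both codings fill the range 40 to 160, so a range check passes either way. The second-person validation under Data management concerns data entry, which does not test scoring direction.

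**5. Sample size.** A two-sample t-test with d = 0.5, two-sided alpha 0.05 and power 0.80 needs 64 per arm, or 128 in total; 128/(1 − 0.12) = 145.5, rounded up to 146. This is the protocol's figure. (The normal approximation gives 63 per arm, and 126/0.88 = 143.2, rounded up to 144.) At 64 per arm, power by the normal approximation is 0.807 for d = +0.5 and 0.807 for d = −0.5. The scoring question leaves the sample size, alpha and power untouched.

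**The case against.** The strongest reply is that the sentence is ambiguous rather than reversed. It states an anchor order and also a direction. A reversed result needs three things together: the printed anchors govern data entry, no item is recoded, and the team still reads a high total as good. The article shows neither of the first two. It describes an existing scale by citation, and item-level scoring is often left to the instrument's guide or the full protocol, so the lack of a stated recoding step is not a fault in itself. An error of this kind is also recoverable: if all items share one coding, subtracting the total from 200 restores it with no loss of data. The scale has an exercise domain, so a flipped score might show up as an unexpected association with step counts or the activity questionnaire.

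All of this stands as a limit on the consequence. It does not remove the contradiction, which no other section resolves. The cross-check against activity measures is possible, but the article does not plan it.

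Two stronger readings are tempting and not supported.
- A reader might infer that the trial would show significant harm in about 80% of repetitions. That is only the planned power with its sign changed. It presumes that miscoding occurs and that the true HPLP-II effect is 0.5 SD. Study sample takes 0.5 from a review of effects on healthy lifestyle ("a medium effect size of 0.5 (with 80% power and .05 significance) is conservatively adopted in this study") and does not tie it to this scale.
- A reader might infer that the interview sample under Process evaluation would be spoiled. That sampling draws on low, middle and high changes across the primary outcomes, so both extremes and the middle would still be covered if one scale were flipped.

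**Conclusion.** The contradiction is certain and follows from one sentence, without any outside source: the printed anchors with a plain sum make higher totals worse, and the text calls them better. Whether any result would be reversed is not known. If the anchors are applied without recoding and the total is read as stated, the HPLP-II effect changes sign at unchanged size and p-value. If the anchors were printed in the wrong order and the scoring syntax is right, only the wording needs correction. It would go beyond the document to say that the trial's scoring is reversed.

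The direction argument assumes positively worded items under a common coding, as the description of the scale implies. Because this is the scoring rule for a primary outcome, it should be settled before any score is computed.

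**What to change.** First check the Chinese instrument form, the data-entry template and the scoring syntax to see how responses are actually coded. Then state one consistent rule:
- if the form is coded in ascending frequency, 1 = never through 4 = always, with the total as the sum of the 40 items that the range implies; or
- if the form is printed from always to never, each item recoded as 5 minus the response before summing (total = 200 minus the raw sum).

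In both cases the range stays 40 to 160 and higher means better. If the check finds items that differ in direction, list them, because the 200-minus rule would then not apply to the total as a whole.

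The cost is one corrected sentence and one check of the syntax, for example by scoring an all-always and an all-never test record and confirming 160 and 40. Recruitment, data collection, sample size, alpha and power are unaffected.

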### Face-to-face preparatory phase

The preparatory phase will be conducted by the nurse researcher prior to the participant’s discharge. It consists of two sessions, with the first session being an individualized health counseling session and the second as a group-based engagement session.

The aim of the individualized health counseling is to identify patients’ self-care needs through a health assessment, develop client-centered goals and a corresponding action plan for lifestyle modification and disease management. The assessment focuses on self-care behaviors for managing CHD including exercise pattern, dietary habits, stress management and tobacco cessation as well as social aspects of disease management such as demographic background, role demand and social support to identify self-care needs. Patients’ function capacity will be assessed by submaximal test using remote electrocardiography (Mindray Tel-200, China) monitored six-minute walk test, based on which the metabolic equivalent (MET) will be calculated by the nurse [46, 50]. Accordingly, the nurse will provide brief health counseling based on the international guidelines recommendations for CR. The discrepancy between the patients’ self-reported behaviors and the guideline recommendation will be highlighted, and the impact of this on health outcomes will be elaborated upon. By increasing the participants’ awareness of their own self-care deficits, the nurse will support them in developing their goals for improving exercise patterns, dietary behaviors, and stress management.

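### The smoking questions carry no reference period and are first asked in hospital, so patients who stopped at admission can enter as ex-smokers and the endpoint need not capture maintained quits

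*Protocol article*

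**What the plan says.** The Primary outcomes section of the protocol article lists smoking among the primary outcomes: "The primary outcomes focus on health behavioral change including physical activity, health promoting lifestyle habits, and smoking behaviors". It prints the instrument in full. "Smoking status will be asked to evaluate the abstinence rate using two questions": the first is "what is your current smoking status? (current smoker, ex-smoker or nonsmoker", the second "How many cigarettes do you smoke per day". Neither item has a look-back window, a minimum length of abstinence or a reference to smoking before admission.

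On timing, Study sample recruits inpatients: "Eligible participants will be identified by research nurses from four inpatient cardiac departments of the hospital by reviewing medical records". It continues: "After obtaining informed consent, baseline data will be collected". Randomization and data collection procedure places the allocation envelope after T0, with follow-up at 6 weeks (T1) and 12 weeks (T2). Face-to-face preparatory phase states: "The preparatory phase will be conducted by the nurse researcher prior to the participant’s discharge".

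On analysis, Data analysis states that "the Chi-square test will be used to compare the number of patients who quit smoking between the groups", and adds a Friedman test on the percentage of cessation over time. It does not say who counts as having quit or what the denominator is.

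**The concern.** The patients are in hospital for a first diagnosis of coronary heart disease or an exacerbation. Some of those who smoke may stop on admission. For them, the relevant result of a post-discharge programme is whether the stop lasts. A question about current status, asked on the ward, can place them in the same category as someone who stopped years ago.

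The follow-up assessments have the matching weakness. With no required period, a patient who stopped the day before T2 and one who has not smoked since discharge give the same answer. The stated aim is an abstinence rate, but the rate is tied neither to a defined group of smokers nor to a defined period of abstinence.

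**Working it through.** **1. Where T0 falls.** Participants are identified as inpatients, consent, and give baseline data. Allocation is disclosed only after that, and the first intervention sessions come before discharge. T0 is therefore answered in hospital. It is also answered before anyone knows the arm.

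**2. What the printed items record.** Two readings of *quit* are open. Reading A: current smoker at T0 and not at follow-up. Reading B: any ex-smoker at follow-up. The last column is the outcome proposed under the fix.

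| Patient | T0 answer | T2 answer | Reading A | Reading B | 7-day abstinence among pre-admission smokers |
|---|---|---|---|---|---|
| Smoked until admission, stays stopped | may be ex-smoker | ex-smoker | outside the count | quit | abstinent |
| Smoked until admission, relapses | may be ex-smoker | current | outside the count | not quit | not abstinent |
| Stopped years ago | ex-smoker | ex-smoker | outside the count | quit | not in the population |
| Current smoker at T0, stopped the day before T2 | current | ex-smoker | quit | quit | not abstinent |

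Reading A cannot tell the first two rows apart. Reading B cannot tell the first from the third. Both accept the fourth.

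**3. The plan's own sample size.** With d = 0.5, 80% power and two-sided 5%, the two-sample t-test needs 63.77, so 64 per arm and 128 in total. Then 128 / 0.88 = 145.5, which rounds up to 146 as stated. This figure is not in dispute. It rests on a healthy-lifestyle effect size, not on smoking.

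**4. Illustration of size.** The documents give no smoking prevalence and no rate of stopping at admission, so every smoking input below is an assumption. Equal allocation (146 / 2 = 73 per arm) is also assumed.

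- Pre-admission smokers at 30% to 50%: 73 × 0.30 = 21.9 and 73 × 0.50 = 36.5 per arm.
- Answering ex-smoker at T0, 15% to 45%: 21.9 × 0.15 = 3.3 and 36.5 × 0.45 = 16.4 per arm leave the count under reading A.

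For precision, take 64 evaluable per arm, widen the share answering ex-smoker, and assume abstinence of 40% v 60% in whoever is counted:

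| Share answering ex-smoker | Counted per arm (30% smokers) | Power | Counted per arm (50% smokers) | Power |
|---|---|---|---|---|
| 0% | 19.2 | 0.23 | 32.0 | 0.36 |
| 25% | 14.4 | 0.18 | 24.0 | 0.28 |
| 50% | 9.6 | 0.13 | 16.0 | 0.20 |
| 75% | 4.8 | 0.09 | 8.0 | 0.12 |

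Power is low throughout. The reclassification lowers it further.

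**5. How much of an effect goes uncounted under reading A.** Let f be the share answering ex-smoker, a the risk difference in them and b the risk difference in those still smoking at T0. The uncounted share is f·a / (f·a + (1 − f)·b).

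- With a = 0.20 (50% v 70%) and b = 0.10 (20% v 30%): f = 0.25 gives 0.05 / 0.125 = 40%; f = 0.50 gives 0.10 / 0.15 = 67%; f = 0.75 gives 0.15 / 0.175 = 86%.
- With a = b the share is simply f: 25%, 50% and 75%.

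The higher figures thus depend on assuming a larger effect in recent quitters.

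**The case against.** The strongest reply has four parts.

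First, quit is undefined and status is asked three times. A T0 ex-smoker who relapses is recorded later as a current smoker, so the data are not lost. The Friedman analysis might register the change, depending on how cessation is coded. This stands. A reader might infer that the planned analysis necessarily misses relapse; the documents support that only under reading A. But reading B admits long-term ex-smokers, so neither reading gives abstinence among people who smoked up to the event.

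Second, the article is a condensed text and cites a source for the two items. That source or the questionnaire might define ex-smoker or instruct interviewers. This is possible and cannot be checked here. However, the article prints both items in full, and used as printed they give the weaker endpoint. Elsewhere it does state reference periods: DASS-21 covers the past week and step counts cover three weekdays.

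Third, an inpatient a few days into admission may still answer current smoker and give his usual number. The preparatory phase does expect to find participants who smoke. This stands, and it is why the point is that patients can be misrecorded, not that they will be.

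Fourth, a reader might infer a pull toward no effect. T0 precedes allocation, so the misclassification is balanced in expectation. Removing recent quitters costs precision and changes the population. It does not by itself shrink the contrast among those who remain. A reader might equally infer a bias in favour of NeCR, since participants are unblinded and the web platform shows smoking in red and quitting in green. That display is a self-monitoring feature, not the outcome measure. The outcome assessors are blinded, and the limitations section already acknowledges social desirability bias. Neither direction is established.

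**Conclusion.** The point holds as a weakness of measurement in a primary outcome. As printed, the items let patients who smoked until admission enter as ex-smokers, and let a stop of any length count as abstinence at T1 and T2. What follows for the quit count depends on a definition the article does not give, but both natural definitions fall short. The main harm is lost precision and an endpoint that does not capture maintained admission-triggered quits as such.

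Size and net direction of bias cannot be determined from the documents. The figure of about 3 to 16 smokers per arm leaving the count, and the uncounted shares of effect, rest wholly on assumed prevalences, reporting rates and abstinence rates, and apply to reading A. The sample size of 146 is unaffected. This is a worthwhile, inexpensive improvement.

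**What to change.** - At T0, ask whether the patient smoked at all in a stated period before this admission (for example 30 days), and how many cigarettes per day in that period. Anyone answering yes is a baseline smoker.
- At T1 and T2, ask whether the patient has smoked at all in the past 7 days.
- Define the smoking outcome as 7-day abstinence at T2 among pre-admission smokers, with relapse counted as not abstinent, and state this population as the denominator in Data analysis.

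The 30-day and 7-day windows are suggestions; what matters is that each is stated. The T0 change must be in place before baseline collection, because smoking before admission is hard to recover reliably afterwards. The cost is two reworded items, with no extra visit, staff or procedure. The small downside is a departure from the cited wording, which can be met by keeping the two printed items alongside.
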